## Abstract

**Background:**

Symptom burden remains a critical concern for individuals with non-small cell lung cancer (NSCLC) following the completion of treatment. The most common symptom clusters, dyspnea (shortness of breath) and fatigue, can contribute to physical decline, reductions in quality of life, and a higher risk of comorbidities and mortality. Dyspnea is a primary limiter of exercise capacity in individuals with lung cancer, resulting in exercise avoidance and an accelerated physical decline. As such, designing resistance training with cluster sets to mitigate symptoms of dyspnea and fatigue may result in improved exercise tolerance. Thus, maintaining the exercise stimulus via cluster sets, combined with improved tolerance of the exercise, could result in the maintenance of physical function and quality of life. The purpose of this study is to investigate the feasibility and preliminary efficacy of a hybrid-delivery home-based cluster-set resistance training program in individuals with NSCLC.

**Methods:**

Individuals with NSCLC (*n* = 15), within 12 months of completion of treatment, will be recruited to participate in this single-arm feasibility trial. Participants will complete 8 weeks of home-based resistance training designed to minimize dyspnea and fatigue. The hybrid delivery of the program will include supervised sessions in the participants’ home and virtual supervision via video conferencing. The primary outcome of feasibility will be quantified by recruitment rates, retention, acceptability, and intervention fidelity. Exploratory outcomes (dyspnea, fatigue, quality of life, physical function, and body composition) will be assessed pre- and post-intervention.

**Discussion:**

This study will provide important data on the feasibility of delivering this intervention and inform procedures for a future randomized controlled trial.

**Trial registration:**

Record not yet public

## Background

Advances in the detection and treatment of lung cancer have resulted in an increasing number of individuals living beyond treatment [1]. Unfortunately, individuals with lung cancer are also burdened by clusters of symptoms, most typically dyspnea (shortness of breath) and fatigue [2, 3]. These symptoms contribute to reductions in physical activity and an accelerated trajectory towards physical disability, placing individuals at a heightened risk of developing or exacerbating comorbidities such as chronic obstructive pulmonary disease and cardiovascular disease [4, 5]. In particular, symptom clusters of dyspnea and fatigue have been recognized as a contributor to the reduction in exercise capacity in individuals with cancer [6, 7]. Importantly, poor exercise capacity is associated with exercise avoidance, functional decline (i.e., worse 6-min walk test score), poor prognosis, and lung cancer mortality [8]. Consequently, there is increasing emphasis on exercise capacity as an important outcome in the management of the disease [9].

The configuration of resistance training (RT) sessions may be designed in a way to mitigate symptoms of dyspnea and fatigue, while maintaining sufficient RT stimulus to improve exercise capacity in individuals with lung cancer. Traditionally, RT prescription for individuals with cancer has included multiple sets of consecutive repetitions ranging anywhere from 6 to 15 [10]. It has been suggested that performing consecutive repetitions may result in excessive fatigue, and thus perception of fatigue, which may negatively impact affective responses and motivation for exercise training [11]. Given the debilitating effects of dyspnea in individuals with lung cancer and the proposed influence of dyspnea on exercise capacity, there is a strong rationale to investigate strategies aimed at minimizing dyspnea during exercise in this population [6].

Cluster sets generally refer to the inclusion of intra-set rest periods (i.e., additional rest during the set itself) [12]. Essentially, cluster sets may allow for reduced levels of fatigue at similar loads of training or enable individuals to perform a greater volume/quantity of training with similar levels of fatigue. Prior research demonstrates that RT with intra-set rest results in the attenuation of fatigue that accompanies consecutive repetition protocols (when training loads are equated), resulting in lower perceptions of effort in comparison to traditional configurations [13–15]. Thus, there is potential for cluster sets to result in lower levels of dyspnea and fatigue, which could facilitate greater exercise tolerance and adaptations in physical function and symptom clusters in individuals with lung cancer.

Home-based exercise is a promising strategy to overcome traditional barriers of facility-based exercise interventions (e.g., resources, travel, cost, limited hours) [16]. We hypothesize that a hybrid approach of delivering exercise programming both in-person and through video conferencing (i.e., live delivery of program via video conferencing) may address some of the anticipated barriers. The initial presence of an exercise professional could help with the delivery of safe and appropriate exercise, whereas the transition towards a hybrid approach could foster independence and autonomy. Furthermore, the impact of COVID-19 has necessitated creative solutions to traditional in-person training, whereby the hybrid delivery approach can help ensure safe exercise, but also limit risk in a potentially vulnerable group [17].

The aims of this study are to (1) conduct a single-arm study to evaluate the feasibility of a hybrid delivery home-based RT program by measuring recruitment, retention, acceptability, and intervention fidelity among survivors and (2) gather data using a pre-/post-test design, to estimate preliminary intervention effects on (a) reducing sensations of dyspnea and (b) improved fatigue, physical function and body composition, and quality of life among survivors immediately post-intervention.

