## Methods/design

This is a single-arm feasibility trial evaluating the effects of an 8-week hybrid delivery of RT with individuals treated for NSCLC. The primary outcome of feasibility will be assessed via recruitment, retention, and intervention fidelity (outlined below). Additional outcomes include health/wellness (dyspnea, fatigue, quality of life), muscular strength (5 repetition maximum and 5 times sit-to-stand), body composition (dual-energy X-ray absorptiometry), and exercise capacity (6-min walk test). Outcomes will be assessed pre-/post-intervention. A convenience sample (*n* = 15) will be recruited to determine the feasibility of the intervention. The sample size was determined based on the recommendations from Julious et al. that justify a minimum of *n* = 12 based on feasibility, gains in precision surrounding the mean and variance, and ability to estimate parameters for future studies [18]. Consequently, in line with other exercise oncology trials and in anticipation of an ~75% retention rate, we aim to recruit 15 individuals to participate. The trial is under review at clinicaltrials.gov and deviations to the protocol or trial procedures will be reflected there and reported in the final manuscript. This study is approved by the University of South Carolina’s Institutional Review Board (Pro00110261). An overview of the study scheme is presented in Fig. 1.

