### Participants

Individuals diagnosed with NSCLC stages I–III who have completed their primary cancer treatments within 12 months and have obtained a medical clearance (from a general practitioner or medical team) to engage in RT will be recruited. Participants will be excluded if they (1) have a diagnosis of advanced (stage IV) lung cancer or diagnosis of small cell lung cancer; (2) are not comfortable having study staff visit their homes for RT sessions; (3) have any neuromuscular, cardiovascular, or psychological condition (assessed using self-report questions during eligibility screening) precluding safe exercise; (4) have participated in structured RT ≥ 2 times/week for the past 6 months; or (5) are unable to read/understand English. Further description of eligibility criteria is provided in Table 1.

**Table 1 Tab1:** Eligibility criteria

**Inclusion criteria**	• Completed definitive treatment for localized NSCLC (stages I–III) within 12 months of completion • Has access to stable Internet access for Zoom participation • Willing to complete an 8-week, home-based intervention program that includes face-to-face and Zoom interaction • Willing to consider behavior change at this time • Able to speak and read English • Capable of informed consent • Has obtained medical clearance from a medical practitioner or medical team
**Exclusion criteria**	• Individuals with a known diagnosis of advanced lung cancer (stage IV; due to potential added burden) or diagnosis of small-cell lung cancer • Anyone for whom physical activity is not recommended • Are not comfortable having study staff visit their homes for exercise sessions • Have any neuromuscular, cardiovascular, or psychological condition precluding safe exercise • Have participated in structured RT ≥2 times/week for the past 6 months • Are unable to read/understand English

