### Statistical analyses

We will use descriptive statistics (percentages and means [with standard deviations]) to report on feasibility outcomes (e.g., recruitment, retention, fidelity). Means and standard deviations will be reported for assessments of exploratory outcomes at baseline and follow-up [18]. Baseline and follow-up testing will be conducted on a per-protocol basis. Descriptive statistics of secondary outcomes will be reported and used to inform sample size calculations for a future randomized controlled trial and aid in decisions on whether their inclusion in future trials is warranted [18, 34]. Analysis will be performed with raw data and code shared on osf.io.

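### Aim 2 and two related passages claim intervention effects that a single-arm, one-baseline, one-post-test design cannot deliver, and nothing bars the mean change from informing RCT planning

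*Protocol article*

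**What the plan says.** Three places in the protocol article use effect language.

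- Abstract, Background: the purpose is to "investigate the feasibility and preliminary efficacy of a hybrid-delivery home-based cluster-set resistance training program".
- Background, aims: the second aim is to "gather data using a pre-/post-test design, to estimate preliminary intervention effects on (a) reducing sensations of dyspnea". It continues with improvement in fatigue, physical function, body composition and quality of life.
- Methods/design, first sentence: "This is a single-arm feasibility trial evaluating the effects of an 8-week hybrid delivery of RT with individuals treated for NSCLC".

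The design behind these statements is one group, tested once around the start and once at the end of the 8-week program (Study outcomes, Table 3). No control group, repeated baseline or external comparator is described. Entry is open to people "who have completed their primary cancer treatments within 12 months", with no minimum interval since treatment.

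On the expected course, the Background says of dyspnea and fatigue: "These symptoms contribute to reductions in physical activity and an accelerated trajectory towards physical disability". The abstract hopes that the approach "could result in the maintenance of physical function and quality of life".

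On use, the Statistical analyses section reports means and SDs at each time point. It says that the descriptive statistics of the secondary outcomes will be "used to inform sample size calculations for a future randomized controlled trial and aid in decisions on whether their inclusion in future trials is warranted". Under Pre-established criteria for success, the team will weigh the exploratory outcomes together with feasibility when deciding whether to move to an RCT.

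The Limitations section discusses one matter only: no entry threshold for dyspnea or fatigue.

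**The concern.** A pre/post difference in one group estimates within-person change. It equals an intervention effect only if participants would otherwise have stayed the same and repeat testing adds nothing. The article gives no support for the first condition and argues against it, since its rationale is that these people are declining. If so, an unchanged mean could reflect benefit or its absence, and the design cannot tell which. An improved mean could equally contain practice on the walk, sit-to-stand or strength tests.

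The word preliminary does not cure this. It warns of imprecision, whereas the problem is confounding, which more participants in the same design would not remove.

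What is at stake is what the trial may conclude on aim 2, and what passes to the next trial. The article allows these outcomes to inform progression, sample size and outcome selection without saying which statistic may be used.

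**Working it through.** **1. What the design identifies.** For each outcome:

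mean change = intervention effect + natural course + practice effect + regression to the mean

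One arm with two time points gives one equation and at least two unknowns. A control group, a repeated baseline or a defensible external rate could supply another equation, and none is described. Regression to the mean is probably the smallest term, because entry does not depend on a symptom score. It is not ruled out, because volunteers select themselves.

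**2. What the article says about the extra terms.** The Background and abstract describe decline, with no rate and no 8-week horizon. Recovery after treatment is not described, and practice effects are not addressed. The sign of the total is therefore unknown.

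**3. The article's own number.** Methods/design gives a target of 15 from a minimum of 12 and about 75% retention. 12 / 0.75 = 16, and 15 × 0.75 = 11.25 expected completers. The target is thus close to its stated basis, and nothing here depends on the difference. No alpha, power, effect size or SD is stated, so there is no power calculation to reproduce.

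**4. Precision of the change itself.** The 95% half-width of a mean change is t(0.975, n−1) / √n, in units of the SD of change:

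- n = 11: 0.67 SD
- n = 12: 0.64 SD

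This sampling error comes on top of the confounding in step 1.

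**5. Illustration of the consequence.** All inputs are assumed. Suppose the observed change is 0.5 SD and a later RCT compares mean change between two arms, with a common SD, the same drift in both arms, two-sided 5% and 80% power. Per arm:

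n = 2 × (1.96 + 0.842)² / d²

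d = 0.5 gives 62.8, so 63. True effect = 0.5 − drift, where positive drift is improvement without training.

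| Assumed drift (SD) | True effect (SD) | Needed per arm | Power at 63 per arm |
|---|---|---|---|
| −0.2 | 0.7 | 33 | 98% |
| −0.1 | 0.6 | 44 | 92% |
| 0 | 0.5 | 63 | 80% |
| +0.1 | 0.4 | 99 | 61% |
| +0.2 | 0.3 | 175 | 39% |
| +0.3 | 0.2 | 393 | 20% |

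A true effect of 0.3 SD against a decline of 0.3 SD would show as zero change. These rows show how sensitive planning is to a quantity that the trial cannot measure. They do not correct a number in the plan.

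**The case against.** The other side has a good deal of substance. The trial is openly single-arm, feasibility is primary, the outcomes are called exploratory, and the analysis is descriptive with no test or efficacy threshold. The pre-set success criteria are recruitment, retention and fidelity, and the Discussion ties progression to those plus acceptability. Lack of a control arm is normal at this stage, and SDs from one arm are proper planning inputs. All of this stands, and no control arm is asked for.

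A reader might infer several stronger things that the documents do not support.

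- *That the mean change will be the RCT effect size.* The article says only that descriptive statistics will inform the calculation, and that could mean the SD alone. The gap is that the mean is not excluded.
- *That an outcome will be dropped if its mean does not move.* No such rule exists. The statistics are only to help with the decision.
- *That maintenance was the hypothesis.* The abstract mentions maintenance, but aim 2 speaks of reducing dyspnea and improving the other outcomes.
- *That recovery after treatment will inflate the change.* An entry window with no lower limit makes this possible, but recovery appears nowhere in the article. The mailing, telephone, decision and clearance steps also make entry straight after treatment less likely.

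What does not fall away is the effect wording in three places, the silence of the limitations section on the comparator, and the unrestricted downstream use. None of these is a detail that an article would normally leave to a fuller document, because the article states its aims, uses and limitations itself.

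**Conclusion.** The point holds as a mismatch between claim and design. The article says that it will estimate intervention effects and preliminary efficacy, and the design can only describe change over 8 weeks. The bias has unknown size and direction. The article's own account of decline is enough to rule out assuming stability, but not to quantify the drift.

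The defect lies in the exploratory aim and in what may be carried forward from it. The primary feasibility outcome and the target of 15 are not affected. The per-arm range of 33 to 393 rests entirely on the assumed 0.5 SD observed change and drift of −0.2 to +0.3 SD.

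**What to change.** 1. In the abstract purpose, aim 2 and the first sentence of Methods/design, replace the effect and efficacy wording with: describe within-person change and its variability over 8 weeks.
2. In Limitations, state that without a comparator the change cannot be separated from natural course, practice effects or regression to the mean.
3. In Statistical analyses, state that only SDs, completeness and retention from this trial will inform RCT sizing, and that the target difference will come from outside it, for example a minimal important difference.
4. In Pre-established criteria for success and Statistical analyses, state that the mean pre/post change will not decide progression or whether an outcome is kept.

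The SD should be carried forward with its uncertainty. With 12 completers its 95% interval runs from about 0.71 to 1.70 times the estimate (normal data assumed).

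A plot of change against months since treatment is optional and descriptive only. With about 11 completers it cannot separate natural course from effect.

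The changes are text only, with no added visits, participants or measurements. The price is a weaker preliminary-efficacy claim and the need to justify the RCT's target difference from another source.

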## Methods/design

This is a single-arm feasibility trial evaluating the effects of an 8-week hybrid delivery of RT with individuals treated for NSCLC. The primary outcome of feasibility will be assessed via recruitment, retention, and intervention fidelity (outlined below). Additional outcomes include health/wellness (dyspnea, fatigue, quality of life), muscular strength (5 repetition maximum and 5 times sit-to-stand), body composition (dual-energy X-ray absorptiometry), and exercise capacity (6-min walk test). Outcomes will be assessed pre-/post-intervention. A convenience sample (*n* = 15) will be recruited to determine the feasibility of the intervention. The sample size was determined based on the recommendations from Julious et al. that justify a minimum of *n* = 12 based on feasibility, gains in precision surrounding the mean and variance, and ability to estimate parameters for future studies [18]. Consequently, in line with other exercise oncology trials and in anticipation of an ~75% retention rate, we aim to recruit 15 individuals to participate. The trial is under review at clinicaltrials.gov and deviations to the protocol or trial procedures will be reflected there and reported in the final manuscript. This study is approved by the University of South Carolina’s Institutional Review Board (Pro00110261). An overview of the study scheme is presented in Fig. 1.

**Fig. 1 Fig1:**
[figure not shown]
Overview of the study design

### Participant recruitment and screening

Recruitment will occur in collaboration with a medical and radiation oncology practice (South Carolina Oncology Associates [SCOA]) closely affiliated with an American College of Surgeons (ACOS)–approved Integrated Network Cancer Program at a large community hospital in central South Carolina. Participants will be recruited by (1) use of cancer registry databases at local health care system’s cancer programs and (2) outreach with various cancer support groups and organizations.

Specifically, a partial waiver of authorization is approved by the local Institutional Review Board so the research team can mail an invitation—a one-page, culturally sensitive postcard that includes a study telephone number and email address (to RSVP or get more information about the study)—to all potential participants identified through the cancer registry database. In the event that recruitment numbers are insufficient, we will work closely with our clinical partners (medical, pulmonary, and nurse navigators) who have pre-established relationships with potential participants. The staff of these offices will recruit potential participants in person as they encounter them in their daily practice. A third recruitment method will use the same invitation from the primary recruitment method; instead of being mailed directly to potential participants, the postcard will be positioned in select physician offices and clinics as well as distributed to support groups and programs for individuals with lung cancer.

Moreover, we will closely monitor the response to mailings and adjust our efforts accordingly. Specifically, mail flyers and invitations will be mailed in batches of 100 potential participants. We will schedule mailings to occur approximately every 4–6 weeks until recruitment goals are met. If recruitment numbers are insufficient, we will increase both the size and frequency of mailings.

Within a week of the first anticipated invitation arrival, telephone contact will be initiated with the recipients by a member of the research team. Over the phone, using a script, the research specialist will screen individuals indicating interest in participating to determine eligibility. Additional follow-up telephone contact will be made after the individual has had adequate time (~1 week) to make a decision and speak with a family member about participating. These telephone interactions are designed to strengthen trust in the research team, build credibility, and increase understanding of the study. During this call, interested individuals will be provided with detailed information about the study purpose/aims, protocol, potential benefits, and risks and be asked to answer further eligibility questions. Individuals who are eligible and remain interested will be asked to provide verification of medical clearance and provide informed consent to participate prior to any study activities.

Pre- and post-intervention data collection will take place at the University’s Department of Exercise Science. Exercise sessions will take place in participants’ homes or other convenient locations. Informed consent will occur prior to baseline testing, where a member of the study team will review the consent form in detail and answer any further questions participants might have. Every effort will be made by study staff to ensure the informed consent is understood in its entirety prior to signing.

